#### Interim testing

The interim testing consists of two appointments; a physical/physiological test day, in which participants undergo ECG, provide blood samples for measurement of BDNF, test physical fitness and strength, and are provided with take-home saliva samplers; and an appointment with a project coordinator, whereby the participant completes questionnaires and returns the saliva samplers.

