### Power analysis and statistical analysis

Power estimates were calculated using the G* Power 3 programme [103]. Treatment effects will be investigated by an intention-to-treat approach to data analysis using a hierarchical linear model, whereby therapists will be included at the second level to account for potential nesting by this factor. Power analysis for effects are estimated with conservative repeated measures analysis of variance (ANOVA) (within-between interactions). For the primary outcome measure, based on previous studies [22, 28], the difference in effect size is set to *d* = 0.35, alpha = 0.05, correlation between repeated measures 0.5, two measurements (pre/post), a total of 70 subjects (*n* = 35 in each group) yielding power above 0.82. Moderators and mediators will be investigated using linear multiple regression, fixed model, single coefficients. An effect size set to *f*^*2*^ = 0.15, two-tailed tests, alpha = 0.05 and *N* = 70 yields power above 0.95 with four predictors. For the subset of functional MRI (fMRI) assessments the following statistics and power analysis will be applied: task-fMRI data will be analysed using General Linear Model in SPM12 for pre-processing and single subject and group analyses, GIFT [104] to investigate the functional and structural data, and arterial spin labelling (ASL) data will be analysed in SPM12. Region of interest (ROI) will be analysed for both structural and functional data (SPM12) to extract blood oxygen level dependent (BOLD) responses to test correlation with specified variables. Expecting percent signal changes of approximately 0.5% at the single voxel and spatial smoothing at full width at half maximum (FWHM) of 5 mm (provides an estimated effect size of *d* = 0,7), using the two-tailed independent samples *t* test, an allocation rate of 1, alpha set to 0.05, correlation between repeated measures 0.5 and a total sample size of 80 (40 in each group) yields power above 0.87. For differences between pre-treatment and post treatment data using the same parameters, the matched-pairs *t* test with 20 subjects yields power above 0.90. Treatment effects are estimated using conservative repeated measures ANOVA (within-between interaction), and conservatively setting the estimated value of *d* = 0.35, alpha set to 0.05, two measurements (pre, post), correlation between repeated measures 0.5, and 60 subjects (*n* = 20 per group) yields power above 0.83. Based on these calculations, the estimated power values indicate that risk of committing type II errors is adequately controlled.

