## Discussion

Older adults are a rapidly increasing group. GAD is frequent in this segment of the population, and older patients with GAD often do not receive adequate and effective help through the current healthcare systems, due to priorities favouring younger adults or because of the absence of proper healthcare programmes. Comorbid somatic and psychiatric illnesses are common in GAD, and create a socioeconomic burden [7]. Thus, it is also highly socioeconomically relevant to develop effective treatment for older adults. More importantly, effective treatment can lead to an increase in quality of life for the individual suffering from a psychiatric disorder, as well as improving comorbid somatic disorders. As far as we know, the knowledge on augmented treatment for older adults with GAD is scarce, although previous studies have yielded promising findings. As GAD is prevalent in older adults, and the impact of treatment for this disorder seems reduced with age, it is essential to develop more effective interventions for this growing segment of our population. To the best of our knowledge, no previous studies have investigated CBT augmented with physical exercise in older adults with GAD.

The aim of the present study is to compare the effects of CBT combined with either physical exercise or telephone call attention placebo. We expect that participants receiving CBT + PE will have greater symptom reduction assessed by the PSWQ than participants receiving CBT + AP. Further we expect physical exercise to be an efficient add-on treatment strategy for older adults with GAD because of the benefits of physical exercise on cognitive functions, mediated by changes in BDNF and HRV. We do not expect telephone calls to affect cognitive functions through these mediators, although adding telephone calls to CBT might provide a placebo effect. With the telephone calls, we try to control for the added human contact in the physical exercise condition. The added attention could increase the participants’ focus on the CBT, and as such enhance the treatment efficacy. However, we take great care not to focus on therapeutic content, and kindly ask the participant to discuss the therapy with their CBT therapist, if they bring up CBT-related themes or questions. We also instruct the physical exercise therapists to refer to the CBT therapists for CBT-related question and themes.

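### The power given for the moderator and mediator regression is too high (0.89 on its own inputs, not above 0.95), and it covers one coefficient, not an indirect effect

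*Protocol article*

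**What the plan says.** The section Power analysis and statistical analysis of the Protocol article names its software: "Power estimates were calculated using the G* Power 3 programme". It then says: "Moderators and mediators will be investigated using linear multiple regression, fixed model, single coefficients". The inputs are an effect size f² of 0.15 and "two-tailed tests, alpha = 0.05". The stated result is that N = "70 yields power above 0.95 with four predictors". The section ends by concluding, from all its power values together, that the risk of type II error is adequately controlled.

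Mediation is one of the trial's declared interests. The Discussion expects exercise to help through its benefits on cognitive function, "mediated by changes in BDNF and HRV". The article gives no separate power for an indirect effect.

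**The concern.** Every input needed to check the figure is printed beside it, so the claim can be tested directly, and it does not reproduce. A reader of a null moderator or mediator result would take the chance of having missed an effect of the assumed size to be under 5%. On the stated inputs it is about 11%.

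The article also attaches this one figure to moderators and mediators alike. A moderator can be tested by a single coefficient, so the calculation is of the right kind there. A mediated effect is made of two paths, and the power for one of them is not the power for the whole. Read as the power for mediation, the figure would be overstated further.

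**Working it through.** **Inputs**, all from the section Power analysis and statistical analysis: f² = 0.15; alpha = 0.05, two-tailed; N = 70; k = 4 predictors; test of a single coefficient in a fixed-model linear regression. Stated power: above 0.95.

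**Step 1. Check that the approach matches the article elsewhere.** For the primary outcome, the article uses a within-between interaction with d = 0.35, two groups, two measurements, correlation 0.5 and N = 70. Then f = 0.35/2 = 0.175, and λ = f² × N × 2/(1 − 0.5) = 0.030625 × 70 × 4 = 8.575. With F(1, 68), power is 0.823, which agrees with the article's value of above 0.82. Standard noncentral-distribution power therefore reproduces the primary figure.

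**Step 2. Recompute the regression figure.**
- Noncentrality: δ = √(f² × N) = √(0.15 × 70) = √10.5 = 3.24.
- Residual degrees of freedom: N − k − 1 = 70 − 4 − 1 = 65.
- Two-tailed critical value: t(0.975; 65) = 1.997.
- Power = P(|T| > 1.997), with T noncentral t (65 df, δ = 3.24) = **0.891**.
- Cross-check with noncentral F(1, 65), λ = 10.5: 0.891.

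The type II error is 1 − 0.891 = 0.109.

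**Step 3. Look for a reading that gives more than 0.95.**

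| Reading | Power |
|---|---|
| As stated (two-tailed, four predictors) | 0.891 |
| Any number of predictors from 1 to 6 | 0.891 to one unit in the third decimal |
| Normal approximation, two-tailed | 0.900 |
| Cohen's λ = f²(u + v + 1) = 0.15 × 67 = 10.05 | 0.878 |
| Omnibus test of all four predictors | 0.704 |
| One-tailed | 0.941 |
| 0.15 taken as partial R² (f² = 0.15/0.85 = 0.176), two-tailed | 0.933 |
| 0.15 taken as partial R², one-tailed | 0.967 |

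Only the last row exceeds 0.95, and it departs from two stated inputs at once. The one-tailed run comes closest of the single changes. It may be where the figure came from, but that is a guess.

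**Step 4. Power for an indirect effect (illustration).** The article gives no size for either path. Assume that each has f² = 0.15 and that the two tests are independent. With N = 70, the arm-to-mediator path (one predictor) has power 0.891, and the mediator-to-outcome path given arm (two predictors) has power 0.891. The probability that both are significant is 0.891 × 0.891 = **0.79**.

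**The case against.** The strongest reply on the arithmetic is that it changes nothing. A power of 0.89 is above the 0.82 that the article accepts for its primary outcome, N = 70 is the sample size for that outcome, and the analysis is secondary. This stands, and it makes the point minor. It does not make the printed number right.

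On mediation, the wording about single coefficients is the name of a test family in the power software, and it sits in a power paragraph. The two paths of a regression-based mediation analysis are themselves single coefficients. A condensed article may leave the estimator of the indirect effect to a fuller plan. This also stands. What remains is that the quoted power belongs to one coefficient.

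Four stronger readings are tempting, and the documents do not support them:
- *That one significant coefficient will be taken as proof of mediation.* The article states no such decision rule and does not exclude a test of the indirect effect.
- *That the timing of cognitive testing makes cognition unusable as a mediator.* The interim visit described under "The interim testing consists of two appointments" lists no neuropsychological tests. But nothing fixes post-treatment worry score as the outcome for cognition as a mediator, and questionnaires at 6 and 12 months come after post-treatment cognition. BDNF and heart rate variability, the mediators named in the Discussion, are measured at interim.
- *That moderators are to be tested wrongly.* A moderator-by-arm term is a single coefficient, and the article says nothing to the contrary.
- *That the trial is too small.* Two-tailed power of 0.95 would need N = 89 at f² = 0.15, but 0.95 is reported as a result and not set as a target.

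**Conclusion.** The stated power is wrong on its own inputs: 0.89, not above 0.95, an overstatement of about 6 percentage points. This holds for complete data on all 70 participants, as the article's own calculation assumes. No reading faithful to the stated inputs reaches 0.95.

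The figure applies to one coefficient and should not be read as power for a mediated effect. The 0.79 for an indirect effect is only an illustration, since it rests on assumed path sizes and independent tests. It is not an estimate of this trial's power for mediation.

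Severity is minor. For a single coefficient with complete data, 0.89 still supports the article's conclusion that type II error is adequately controlled. No sample size or analysis changes.

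**What to change.** In Power analysis and statistical analysis, make two changes of wording:

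1. Replace the claim of power above 0.95 with 0.89 (single coefficient, f² = 0.15, two-tailed alpha 0.05, four predictors), and state that this assumes complete data on all 70 participants.
2. Add that this power covers one regression coefficient, such as one moderator term or one path, and does not cover an indirect effect.

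The cost is a sentence or two. No extra participants, measurements or analyses are needed.

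### The power for moderators and mediators is 0.89 on the protocol's own inputs, not above 0.95, and the unjustified f² = 0.15 implies a moderator stronger than the plan's own treatment effect

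*Protocol article*

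**What the plan says.** All of this stands in the protocol article, section Power analysis and statistical analysis.

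- Method: "Moderators and mediators will be investigated using linear multiple regression, fixed model, single coefficients".
- Inputs: f² is set to "0.15, two-tailed tests, alpha = 0.05 and" N = 70. The result is said to be a design that "yields power above 0.95 with four predictors". No source or rationale is given for 0.15, and no interaction term is named.
- Primary outcome: "the difference in effect size is set to" d = 0.35, with reference to earlier studies. The model is "conservative repeated measures analysis of variance (ANOVA) (within-between interactions"), with "correlation between repeated measures 0.5, two measurements (pre/post), a total of 70 subjects" (35 per arm) and a stated power above 0.82.
- Conclusion from all the calculations together: "the estimated power values indicate that risk of committing type II errors is adequately controlled". Moderators and mediators are not excepted.

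**The concern.** Two things look wrong. The stated power does not seem to follow from the stated inputs. And the effect size behind it has no anchor, although the same paragraph fixes a treatment effect against which a moderator can be judged.

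A moderator of the treatment effect is tested by the arm × moderator coefficient. Interactions are usually harder to detect than main effects, yet here the moderator analysis is credited with more power (above 0.95) than the primary comparison (above 0.82) at the same N. If the figure is taken at face value, and the closing sentence on type II error with it, a non-significant moderator could be taken as evidence that the benefit of exercise does not depend on that variable.

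**Working it through.** **1. The stated figure on its own inputs.** Two-tailed t test of one regression coefficient: error df = 70 − 4 − 1 = 65, noncentrality δ = √(f² × N) = √(0.15 × 70) = √10.5 = 3.24, critical value 1.997.

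| Variant | Power |
|---|---|
| As stated: two-tailed, four predictors | 0.891 |
| Two-tailed, one to five predictors | 0.891 throughout |
| F test for the R² increase, one tested predictor | 0.891 |
| One-tailed, four predictors | 0.941 |
| Omnibus R² test, four predictors | 0.704 |

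None exceeds 0.95. Two-tailed power of 0.95 needs f² of about 0.19 at N = 70, or N = 89 at f² = 0.15.

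**2. What f² = 0.15 means for a moderator.** Take residual SD = 1, arm coded ±0.5, a standardised continuous moderator, and a product term uncorrelated with the other predictors. The product has variance 0.25, so f² = β²/4 and β = 2√0.15 = 0.775 SD of exercise effect per SD of moderator. For a 50/50 binary moderator the product variance is 1/16, so β = 4√0.15 = 1.55 SD between the two subgroup effects.

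**3. The plan's own treatment effect.** For the within-between ANOVA, λ = f² × N × m/(1 − ρ) with m = 2 and ρ = 0.5.

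- With f = d/2 = 0.175: λ = 0.030625 × 70 × 2/0.5 = 8.575 on F(1, 68), power 0.823. This reproduces the stated primary power. In a 2 × 2 layout this f is a between-arm difference in change of 4 × 0.175 = 0.70 SD. At ρ = 0.5 the SD of change equals the SD of a single measurement, so f² on the change score is 0.70²/4 = 0.1225 (also 8.575/70).
- With d = 0.35 read literally as a 0.35 SD difference in change: f = 0.0875, λ = 2.144, primary power 0.303. On the change score, f² = 0.35²/4 = 0.0306.

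**4. Moderator power at N = 70, four predictors, two-tailed alpha 0.05.**

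| Interaction, SD per SD (continuous moderator) | f² | Power |
|---|---|---|
| 0.175 | 0.0077 | 0.11 |
| 0.35 (equals the effect on the literal reading) | 0.0306 | 0.30 |
| 0.68 | 0.116 | 0.80 |
| 0.70 (equals the effect that reproduces 0.82) | 0.1225 | 0.82 |
| 0.775 (the protocol's f² = 0.15) | 0.15 | 0.89 |
| 0.87 | 0.19 | 0.95 |

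For a 50/50 binary moderator the same powers need twice the difference: subgroup effects that differ by 0.70 SD give 0.30, and 1.36 SD give 0.80.

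**5. Ratio of 0.15 to the plan's own effect.** 0.15/0.1225 = 1.2 on the reading that reproduces the primary power; 0.15/0.0306 = 4.9 on the literal reading. With baseline adjustment of the literal effect, f² = 0.0306/(1 − 0.5²) = 0.041, the ratio is 3.7 and the power 0.38.

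**The case against.** A reader might infer that the moderator is assumed to be about five times as strong, in f², as the treatment effect, that its true power is simply 0.30, and that the assumption implies harm from exercise in patients with low moderator values (0.35 − 0.77 = −0.42 SD at one SD below the mean). The document does not support this as an unconditional statement. The primary power above 0.82 reproduces only with a 0.70 SD difference in change. Against that effect the ratio is 1.2, the power is 0.82, and the effect at one SD below the mean is 0.70 − 0.77 = −0.07 SD, practically nil. Whoever takes the low reading must also accept a primary power of about 0.30.

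Three further points carry weight. The sentence covers mediators as well as moderators and names no interaction. Some relations that the article expects, such as baseline BDNF with outcome, are associations between patient variables; for these f² = 0.15 (partial r = √(0.15/1.15), about 0.36) need not be tied to the arm effect. A moderator as strong as the main effect is my yardstick, not the protocol's, and nothing caps an interaction at that size. And the protocol nowhere says that a null moderator result will be read as no moderation.

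These points limit the comparison with the treatment effect. They do not touch the 0.89, which needs no assumption about what is moderated, and they supply no reason for choosing 0.15.

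**Conclusion.** The point holds in two parts. The firm part is arithmetic: on the stated inputs the power is 0.89, not above 0.95. The type II risk at f² = 0.15 is thus about 11%, where the text implies less than 5%.

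The second part is conditional. The unsupported f² = 0.15 corresponds, for a continuous moderator, to about 0.77 SD per SD, which is above the plan's own treatment effect whether that is 0.70 SD or 0.35 SD. For a moderator equal to that effect, power is 0.82 or 0.30 respectively; neither is above 0.95. This rests on an arm × moderator test, equal arms, all 70 participants analysed, a product term uncorrelated with the other predictors, and effects expressed in SDs of change at a correlation of 0.5. Which of the two powers applies depends on a definition of d that the article does not give.

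The primary analysis is affected only through that undefined d. The consequence here is an overconfident statement about the moderator analyses, which should be corrected.

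**What to change.** In Power analysis and statistical analysis:

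1. Replace the stated power with 0.89 at f² = 0.15, N = 70, four predictors, two-tailed alpha 0.05, and give a reason for 0.15 or call it a convention.
2. Add the power of the arm × moderator term on the SD scale, for a continuous moderator: about 0.30 at 0.35 SD per SD, 0.80 from about 0.68, and 0.82 at 0.70. State which definition of d = 0.35 the primary calculation uses, so that the two sets of figures can be read together.
3. Call the moderator analyses exploratory and report each interaction with its 95% confidence interval. A non-significant interaction should not be read as absence of moderation.
4. Take moderators out of the closing sentence that type II error is adequately controlled.

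The cost is wording only: no change to sample size, data collection or the primary analysis. The stated power becomes less favourable.

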
To control for type 1 errors, the secondary clinical outcome inventories will be assessed in two stages, initially together, and if significant they will be analysed separately. Pre-treatment differences on continuous and categorical demographic variables between the two treatments will be assessed using the independent samples *t* test and Fisher’s exact test, respectively. Other changes and differences in continuous variables will be assessed using the repeated and independent samples *t* test, and Fisher’s exact test and McNemar’s test to determine proportional differences between or within groups, respectively. Repeated testing within the same domain will be controlled for multiple testing using the Holm-Bonferroni method [105].

Missing data will be handled within the hierarchical linear model analyses. For analyses where this is not appropriate, last observation carried forward (LOCF) will be applied. For inventories, missing data will be replaced by the mean, provided that no more than 20% of values/item for this measure are missing. If more than 20% of values/item are missing, data will be considered invalid, and will be handled as missing as described. The potential impact of compliance with the different treatment elements will be addressed in separate analyses.

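### The between-group fMRI power is that of one unadjusted test at a single smoothed location, so it does not extend to the SPM12 whole-brain, GIFT or ASL comparisons that the protocol describes

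*Protocol article*

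**What the plan says.** Everything needed is in the protocol article under Power analysis and statistical analysis, which introduces the imaging statistics and the imaging power together.

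- **Analysis.** The task data go through a group model: "task-fMRI data will be analysed using General Linear Model in SPM12 for pre-processing and single subject and group analyses". GIFT is to be applied to functional and structural data, and ASL is to be analysed in SPM12. ROI analyses are planned for structural and functional data; the use given for the extracted signal is "to extract blood oxygen level dependent (BOLD) responses to test correlation with specified variables".
- **Power.** The effect starts from "Expecting percent signal changes of approximately 0.5% at the single voxel" and, with 5 mm smoothing, "provides an estimated effect size of *d* = 0,7". The test is specified by "using the two-tailed independent samples *t* test, an allocation rate of 1, alpha set to 0.05", and the result is "a total sample size of 80 (40 in each group) yields power above 0.87".
- **Multiplicity.** A general rule follows later in the section: "Repeated testing within the same domain will be controlled for multiple testing using the Holm-Bonferroni method". It neither names nor excludes imaging.
- **Conclusion drawn.** After all the power figures, the section states that the risk of type II error is adequately controlled.

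The section names no voxel, region or contrast as the one to which the between-group power belongs.

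**The concern.** A single two-tailed t test at 0.05 describes a comparison at one location chosen in advance. An SPM12 group model ordinarily tests many voxels, and GIFT and ASL add further sets of comparisons. Once such comparisons are corrected for their number, the threshold for each is stricter than 0.05 and the chance of detecting an effect of 0.7 is lower than printed.

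At stake is how the imaging sub-study will be read. If the printed power is taken to cover the whole-brain, GIFT and ASL comparisons, a null map could be presented as adequately powered evidence that exercise has no effect on brain response. The primary outcome, the Penn State Worry Questionnaire, and its power calculation are not affected.

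**Working it through.** **Inputs from the document:** d = 0.7; two independent groups of 40; two-tailed test; alpha 0.05. The same sentence gives a correlation of 0.5 between repeated measures, which plays no part in an independent-samples t test.

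**Inputs assumed:** the number of tests corrected for (2, 3, 4 or 10) and, as a further illustration, a per-test level of 0.001. The document gives neither.

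**Formula.** For n per group, df = 2n − 2 and the noncentrality is d × √(n/2). Power is the probability that a noncentral t variable with these parameters falls beyond ± the critical value t(1 − α/2, df).

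**Step 1: reproduce the printed figure.** With n = 40, df = 78 and the noncentrality is 0.7 × √20 = 3.130. At alpha 0.05 the critical value is 1.991 and power is 0.871. This agrees with the printed figure of above 0.87 and leaves almost no margin over it. The figure is thus the power of one test with no adjustment.

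**Step 2: same effect and same 40 per group, stricter per-test level.**

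| Per-test alpha | Critical value | Power |
|---|---|---|
| 0.05 (as printed) | 1.991 | 0.871 |
| 0.05/2 = 0.025 | 2.285 | 0.799 |
| 0.05/3 = 0.0167 | 2.447 | 0.751 |
| 0.05/4 = 0.0125 | 2.557 | 0.716 |
| 0.05/10 = 0.005 | 2.889 | 0.597 |
| 0.001 | 3.420 | 0.394 |

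Under Holm, 0.05/m is only the first and strictest step. For a given test among m, power under Holm lies between the 0.05/m row and the unadjusted 0.871. With four tests, for instance, it lies between 0.716 and 0.871.

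**Step 3: the figure needed for the fix.** The Participants section and the section on physiological and biological measures both give 40 scanned participants in total. With an even split (an assumption), n = 20, df = 38 and the noncentrality is 0.7 × √10 = 2.214. At alpha 0.05 the critical value is 2.024 and power is 0.578. The fall from 0.871 to 0.578 comes wholly from 80 against 40 scanned participants. That is a separate inconsistency and no part of the size of this point.

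**The case against.** The strongest reply is that a condensed article may leave the region, the contrast and the voxel or cluster threshold to an imaging analysis plan. If such a plan names one primary ROI contrast, a single test at 0.05 is legitimate. This stands as far as it goes: the missing threshold is not the point. But the article prints a power figure and an adequacy conclusion beside a list of analyses, and does not limit either to one test. A later plan that adds a correction would not make the printed figure apply to the corrected comparisons.

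A reader might also infer that maps will be thresholded at an uncorrected 0.05, so that about 5% of null voxels would be declared positive. The document does not support this. In the imaging passage, 0.05 appears only as an input to power, and the Holm rule may cover imaging. If it does, the false-positive side is addressed and the power side of this point is confirmed.

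A third reply is that the section holds two other imaging calculations: a pre-post one ("the matched-pairs *t* test with 20 subjects yields power above 0.90") and a repeated-measures ANOVA with an effect of 0.35, which is the one tied to treatment effects. It would therefore be too strong to say that the imaging power fits no analysis in the plan, and I do not say so. Neither calculation supplies what is missing, since each also uses 0.05 without adjustment.

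Finally, nothing says that the SPM12, GIFT, ASL and ROI analyses form one domain for Holm, and the ROI work is linked to correlations rather than clearly to the arm comparison. The count of four is therefore an illustration only.

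**Conclusion.** The point holds in a limited form. The between-group fMRI power is a per-test figure for one unadjusted comparison at a single smoothed location. It is not shown to be the power of the SPM12 whole-brain, GIFT or ASL comparisons, so the statement that type II error is adequately controlled does not extend to them.

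The direction is certain for any correction that tightens the per-test level. The size is not, because the number of tests is assumed: with 40 per group, 0.80 at 0.05/2, 0.72 at 0.05/4 and 0.60 at 0.05/10. These figures keep the protocol's own d = 0.7, which is not examined here. No inflation of false positives is established. The consequence is confined to the nested imaging study, and the remedy is a matter of wording, although it should be made before the imaging data are analysed.

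**What to change.** In the power and statistics section:

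1. Name one ROI and one flanker-task contrast as the single pre-specified between-arm imaging test, two-tailed at 0.05, using the ROI extraction already planned.
2. State that the between-group imaging power applies only to that test, and recompute it for the number actually scanned. Do not carry the 0.87 over, since it assumes 80 scanned participants. With d = 0.7 kept and 40 participants split evenly, power is about 0.58. Say why an effect derived for a smoothed voxel should hold for an ROI mean, or give a range of effects.
3. Label the SPM12 whole-brain, GIFT and ASL comparisons exploratory, with family-wise error correction and no power claim, and limit the type II error conclusion accordingly.

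No extra scans are needed. The cost is committing to one ROI in advance, giving up the power claim for the remaining imaging comparisons, and printing a less favourable power figure.
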